### Adverse effect monitoring

The stimulation protocol has been reported as safe and suitable for OCD symptom reduction in previous RCTs [39, 40], and there is no anticipated harm and compensation for trial participation. However, if a participant reports any moderate to serious problem, the stimulation will be stopped, and the trial will be discontinued for that participant, and if more than two participants report serious adverse events, the stimulation will be discontinued. According to the ethics committee rules, the trial management group is responsible for providing any necessary medical care due to trial participation.

### Measures

#### Screening measure for tDCS

Antal et al. [43] have provided a comprehensive measure to screen all candidates for tES. The contraindications and high-risk conditions for tES will be listed in a questionnaire, including a history of epilepsy or seizure, having metal or electronic implants in the head, use of a cardiac pacemaker, history of head trauma or head surgery, being pregnant, and history of fainting spells or syncope.

#### Pre-, post-, and follow-up assessments

##### Quantitative electroencephalography (qEEG)

EEG is a non-invasive technique that allows recording the brain’s electrical activity over the scalp. Extracting EEG signal features through mathematical algorithms is called quantitative EEG, an applicable method in research and clinical diagnosis for neurological and psychiatric disorders [49]. For the present study, EEG will be recorded by an EEG equipment amplifier using a 19-electrode cab placed according to the international 10-20 system. EEG recording will be obtained during two resting conditions, including eyes-closed and eyes-open, for at least 3 min for each condition. Participants will be required to avoid caffeine, tobacco, and alcohol from the night before recording. They will be provided with some explanations to be familiarized with the recording procedure before starting. After fitting into the cab, they are asked to sit comfortably and close their eyes for eyes-closed recording. Then, they open their eyes and fixate on the screen with minimum eye blinking for eyes-open recording. The quantitative analysis will be performed by referring recorded data to the database.

##### Cognitive tests

The computerized cognitive tests include the following:Dot-probe test (DPT) assesses attentional bias toward contamination-related stimuli. DPT trials consist of simultaneously presenting two stimuli on the screen. When they disappear, a probe is shown at the location of one of them. Reaction time to the probe change depends on the attentional bias toward one of two pictorial stimuli [50, 51].Emotional Stop-Signal test (ESST) to see to what extent the emotions interfere with inhibitory control. The standard SST is a choice reaction time task in which each of two target stimuli (e.g., a right and a left arrow) correspond with a key press response (e.g., right and left key). Participants should respond as quickly as possible by pressing the corresponding response key (go-trials) and withhold response if the stimulus is followed by a stop-signal (e.g., a tone; stop-trials). The ESST includes emotional stimuli presenting before targets with the assumption that emotion may disrupt inhibitory control [52].Emotional Go/NoGo test (EGNT) to investigate how emotions interfere with response inhibition. The participants are instructed to respond as quickly as possible to go-trials (e.g., a symbol $) and avoid responding to no-go-trials (e.g., a symbol #). By presenting emotion-eliciting stimuli (e.g., before the target stimuli), their interference effect on response inhibition can be explored [53, 54].

The stimuli will be selected from contamination-related pictures (the same CSs of training) that are disgust-eliciting and neutral pictures.

##### Self-report measures

The self-report measures include the following:Padua Inventory-Washington State University Revision (PI-WSUR), a 39-item scale to measure OCD symptoms in 5 subscales, rating on a 5-point Likert scale (0 = not at all, to 4 = very much). It includes ten items for the “contamination obsessions and washing compulsions” subscale [55, 56].Yale-Brown Obsessive-Compulsive Scale (Y-BOCS) that is one of the most applied scales to assess the severity of OCD symptoms; its ten items address the amount of time, interference, distress, resistance, and control for obsessions and compulsions separately. All are rated 0 to 4 [57].Disgust Scale-Revised (DS-R), a questionnaire comprising 25 items that describes common disgust-relevant experiences. The first part (items 1–13) requires answers to true/false choices and the second part (items 14–25) requires a rating on not/slightly/very choices. Core disgust, animal reminder disgust, and contamination-based disgust are the three subscales [58].Beck Depression Inventory-II (BDI-II), the revised version of BDI, consists of 21 items. All items reflect major depression disorder (MDD) symptoms based on DSM-IV and should be ranked on a 4-point scale [59].Beck Anxiety Inventory (BAI), a 21-item scale to rate anxiety symptoms severity on a scale ranging from 0 (not at all) to 3 (severely) over the last week [60].Disgust Rating Scale (DRS), a self-report evaluation in which the participants will rate all 30 CSs in terms of how much they can elicit disgust on a scale from 0 (not at all) to 10 (very much).

BDI-II, BAI, and DS-R scores will be administered once at pre-assessment and will not repeat at post- or follow-up assessments, but others do.

### Expected outcomes

This trial will investigate whether positive EC plus sham or real tDCS has a transfer effect on C-OCD characteristics. Outcomes will be acquired at pre-, post-, and follow-up assessments. Table 1 shows assessment time points and measures.

**Table 1 Tab1:**
[figure not shown]
Procedure schedule

*EC*, evaluative conditioning, *tDCS*, transcranial direct current stimulation, *EEG*, electroencephalography, *DPT*, dot-probe test, *EGNT*, Emotional Go/NoGo test, *ESST*, Emotional Stop-Signal test, *PI-WSUR*, Padua Inventory-Washington State University Revision, *Y-BOCS*, Yale-Brown Obsessive-Compulsive Scale, *DS-R*, Disgust Scale-Revised, *BDI-II*, Beck Depression Inventory-II, *BAI*, Beck Anxiety Inventory, *DRS*, Disgust Rating Scale

The primary outcome measures will be disgust reduction and change in clinical symptoms. We hypothesize that pairing C-OCD-related stimuli with positive USs can reduce disgust feeling toward them in C-OCD patients, and simultaneously cathodal tDCS over left OFC may boost this effect. For that, we will measure the amount of disgust elicited by contaminated stimuli on a Disgust Rating Scale, at baseline and after completing interventions. We will also look for possible transfer effects in OCD symptoms from pre- to post-interventions, measured via PI-WSUR and Y-BOCS. Based on previous studies in which the role of disgust has been implied in the pathology of OCD and the assumption that targeting this negative emotion may have treatment outcomes, it is hypothesized that EC may lead to diminishing C-OCD symptoms, mainly when it is along with cathodal tDCS, over left OFC.

The secondary outcomes include cognitive measures and QEEG recording. Disgust as a negative emotion may affect cognitive functions [61, 62], and OCD patient has been shown to have cognitive deficits in attention, memory, and executive function [63–65]. First, we aim to examine attentional bias and inhibitory control in C-OCD patients when confronted with contaminated stimuli compared with neutral ones. Then, the study will explore whether entering these contaminated stimuli into a positive EC training leads to better performance in these cognitive tests. We are also interested in investigating the correlation of cognitive performance level with the self-reported disgust rating, both at the baseline and after completing interventions. For QEEG recording, we will look for changes in brain wave characteristics from pre- to post-interventions.

We expect a more significant effect for all measures when the EC training is combined with cathodal tDCS than each one alone. We will also detect hypothesized effects at a 2-month follow-up.

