## Methods/design

### Study design and setting

This study is a four-arm, randomized, placebo-controlled clinical trial in which participants get sham or real forms of two interventions, including EC and tDCS. It is aimed to investigate the effectiveness of EC, tDCS, and a combination of both on disgust reduction, clinical symptoms, and cognitive characteristics in C-OCD patients. Randomly assignment will be in blocks of 4 in 1:1:1:1 allocation to four parallel groups: (1) real EC plus real tDCS, (2) sham EC plus real tDCS, (3) real EC plus sham tDCS, (4) sham EC plus sham tDCS. We consider sham interventions to be able to separate the exposure effect from the EC effect and also to monitor the placebo effect. Assessments occur at baseline, after completion of 10 interventional sessions, and in a 2-month follow-up. All groups have similar assessments and equal intervention amounts (equal time, activity, and number of sessions). Figure 1 shows the design of the study. The trial will be conducted in the Cognitive Science Laboratory of Ferdowsi University of Mashhad, Mashhad, Iran.

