### Sample size

We calculated the sample size using the G*Power 3.1 software. To be able to get an effect on our primary outcomes (disgust feeling and clinical symptoms) in three measurements (pre-, post-, and follow-up) at repeated-measure-MANOVA approach, with 95% confidence and 80% power, estimating large effect size with Cohen’s *f* value 0.40, a sample size of 46 participants was calculated. With an attrition rate of 20%, we aim to enroll 55 participants.

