### Statistical analysis

First, data entry will be double-checked. Data quality will be examined regarding data distribution, and outliers will be excluded from further analysis. When these items are ensured, the primary and secondary outcomes will be analyzed in detail using IBM SPSS statistics 25 for Windows (Armonk, NY: IBM Corp). Descriptive statistics (e.g., mean and standard deviation) will be reported for each arm separately. We will conduct the analysis within the intention-to-treat (ITT) framework to investigate the effectiveness of the interventions for all subjects with multiple imputed data sets in case of missing data. The appropriate statistical method will be performed to analyze data. The major one will include mixed and repeated measures of multivariate analysis of variance (MANOVA) to assess the effect of group (arm) and time and their interactions on the result of EEG recordings, computerized tests, and self-report measures as dependent variables. The significant level will be set at 0.05. The covariates, including age, disgust sensitivity, anxiety, and depression, will be considered in the statistical model.

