## Discussion

Considering the central role of disgust in developing, maintaining, and treating OCD, this RCT will explore the potential effect of evaluative conditioning training to reduce disgust in C-OCD patients. The proposed EC training program is a computerized task in 4 difficulty levels using contamination-related pictures (as CSs). The pictures will be about those stimuli that most people with C-OCD are concerned about, experience a high degree of disgust when confronted with, and try to prevent. The study will elucidate whether repetitive pairing of disgusting contamination-related stimuli with pleasant ones can modify the disgust experience in this clinical sample.

We aim to try a new intervention method directly targeting disgust in a computerized framework. The novelty of our protocol is administering such a disgust reduction-focused EC training in C-OCD patients and combining it with a brain stimulation protocol that modulates OFC activation.

We also hypothesize that if the disgust experience is successfully modified in this manner, this may decrease obsessions with contamination and compulsive behavior toward them. So, the study will allow for inspecting any decrease in clinical symptoms of C-OCD after the intervention.

Since disgust experience can cause attentional bias and interfere with inhibitory control, this study will provide information about the assumption that EC training focused on disgust reduction may decrease attentional bias toward them and improve inhibitory control. Besides looking for data based on disgust rating through a conscious self-report, cognitive tests will allow us to investigate some implicit aspects. We will also explore the brain wave characteristics to determine whether there is any change due to interventions.

In sum, this trial will investigate the EC effect alone and in combination with cathodal tDCS over OFC on self-report disgust experience, cognitive functions, and clinical symptoms of C-OCD in such a group of patients. Improving any aspect would lead us to make more effective add-on treatments for OCD.

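### Two primary domains on three unranked scales share one flat 0.05, while the sample size pays for one test; tested separately, the scales carry a 10 to 14% chance of a false primary claim

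*Protocol article*

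**What the plan says.** In the protocol article, the end of the Background and the text under Expected outcomes both label disgust and clinical symptoms as primary: "The primary outcome measures will be disgust reduction and change in clinical symptoms". Disgust is rated on the DRS, and symptom change is "measured via PI-WSUR and Y-BOCS". No scale is placed first, and no rule says whether a positive trial needs one scale or all three.

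The design has four arms: "Randomly assignment will be in blocks of 4 in 1:1:1:1 allocation to four parallel groups". The Background sets out to compare the single interventions with the combination. Expected outcomes predicts that the combination will outperform each component on every measure. The primary change is worded as baseline to post-treatment, and a closing sentence extends the hypotheses to the 2-month visit.

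Statistical analysis names mixed and repeated-measures MANOVA for arm, time and their interactions, then says: "The significant level will be set at 0.05". It gives no order and no adjustment. Sample size refers to the primary outcomes in the plural, "in three measurements (pre-, post-, and follow-up) at repeated-measure-MANOVA approach", "with 95% confidence and 80% power", with a Cohen's f "value 0.40, a sample size of 46 participants was calculated".

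**The concern.** With several primary scales, one significance level and no order between them, a significant result on any one scale can be presented as the trial's primary finding. The chance that at least one is a false positive then exceeds the stated 5%. The claim most exposed is the clinically important one, that OCD symptoms improve, because two of the three scales measure symptoms. The sample size makes no allowance for this. Either the error rate is above 5%, or a correction added later would take power that was never budgeted.

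**Working it through.** **Inputs from the protocol article.** Four arms (Study design and setting); three measurements, f = 0.40, alpha 0.05, power 0.80, N = 46 (Sample size); three primary scales (Expected outcomes); level 0.05 (Statistical analysis). The article gives no correlations between scales or visits, so those below are assumptions shown as ranges.

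**1. Reproduce 46.** Repeated-measures MANOVA, group-by-time interaction, Pillai statistic, k = 4 groups and m = 3 measurements:
- s = min(k − 1, m − 1) = min(3, 2) = 2
- df1 = (k − 1)(m − 1) = 3 × 2 = 6
- df2 = s(N − k) = 2 × (46 − 4) = 84
- noncentrality = N × s × f² = 46 × 2 × 0.16 = 14.72
- power = 0.8015, and 46 is the smallest N that reaches 0.80

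The between-groups version gives 50 at a correlation of 0.5 and 41 at 0.3, so the interaction is the version that matches. The figure pays for one test at 0.05.

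**2. Three scales tested separately, one contrast, one visit.** If independent: 1 − 0.95³ = 1 − 0.857 = 0.143. With correlated two-sided z statistics (400,000 simulated draws):

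| Correlation between scales | Chance of at least one false claim | Multiple of 0.05 |
|---|---|---|
| 0 | 0.143 | 2.9 |
| 0.5 | 0.126 | 2.5 |
| 0.8 | 0.099 | 2.0 |

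**3. If more tests also count as primary.** The lower figure in each range assumes a correlation of 0.8 between scales and between visits; the upper figure assumes independence.
- Three scales, two visits, one contrast (6 tests): 0.15 to 0.26
- Three scales, two visits, two main effects (12 tests): 0.28 to 0.46
- Three scales, two visits, three factorial contrasts (18 tests): 0.38 to 0.60

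**4. If the three scales enter one joint MANOVA.** One interaction test has error 0.05 when no scale changes. Suppose DRS truly changes and makes the joint test significant. PI-WSUR and Y-BOCS are then each tested at 0.05, with no true effect on either. The chance of at least one false symptom claim is 1 − 0.95² = 0.0975 if they are independent and 0.078 at a correlation of 0.8.

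**5. What each remedy costs, on the plan's own sample-size method.**

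| Approach | Alpha for first test | Power at N = 46 | N for 80% power |
|---|---|---|---|
| As planned, one test | 0.05 | 0.80 | 46 |
| Bonferroni over two domains | 0.025 | 0.71 | 54 |
| Bonferroni over three scales | 0.05/3 = 0.0167 | 0.65 | 58 |
| Fixed sequence | 0.05 | 0.80 | 46 |

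**The case against.** The strongest reply is that the article never says each scale, contrast and visit is a separate primary test. The named method is MANOVA, and 46 reproduces as one omnibus test. One joint group-by-time test would cover all three scales and both later visits at 5%. Multiplicity rules and the grouping of dependent variables are also often left to an analysis plan, which is not shown here.

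Part of this stands: the inflation is conditional on how the tests are run. It does not remove the point. A significant joint test does not say which scale, arm or visit changed, and the aims need exactly that. Step 4 shows that protection is lost once DRS responds. The article itself fixes two primary domains and one flat level, so this is a stated rule with a poor error rate and not only an omitted detail.

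Three stronger readings are tempting but not supported:
- **A definite multiple of the nominal error.** The multiple runs from 1 (one joint test under the global null) to about 12 (0.60/0.05, all 18 tests independent). The article does not settle which applies, nor whether the 2-month visit is co-primary.
- **An any-aspect success rule.** The Discussion says "Improving any aspect would lead us to make more effective add-on treatments for OCD". This is a closing remark about developing treatments. Its context includes cognitive functions, which are secondary, and it sets no criterion for a positive trial.
- **An impossible pooled MANOVA.** A reader might infer that EEG, cognitive and self-report variables all enter one model with too few residual degrees of freedom. The article lists these outcome types under one method without saying they share a model. Counting only completers would also ignore its intention-to-treat analysis of all subjects with multiple imputation.

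**Conclusion.** The concern holds in a limited form. The protocol article fixes two primary domains on three unranked scales and one unadjusted 0.05, with a sample size that pays for a single test. Separate testing of the three scales, for one contrast at one visit, gives about a 10 to 14% chance of at least one false primary claim. A joint MANOVA followed by separate tests gives about 8 to 10% on the two symptom scales when DRS truly changes. The lower ends assume a correlation of 0.8 and the upper ends independence. Further contrasts and the 2-month visit would raise these figures, by an amount the document does not determine.

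**What to change.** In Expected outcomes and Statistical analysis:
1. Name one primary contrast and one visit, for example the EC effect on change from baseline to post-treatment.
2. Test the scales in fixed order, each in its own model at 0.05: DRS, then PI-WSUR, then Y-BOCS. Confirmatory claims stop at the first non-significant step. The order follows the article's own hypothesis that reduced disgust leads to fewer symptoms.
3. Report the tDCS effect, the combination contrasts and the 2-month visit as pre-specified secondary analyses that do not depend on the EC result.
4. Report cognitive and EEG results as secondary, without confirmatory claims.

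Record the order, with a date, before outcomes are compared between arms. Restate power for the named contrast, because 46 belongs to the six-degree-of-freedom omnibus test.

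The cost is wording. The sequence adds no participants and leaves the first test its full 0.05, whereas Bonferroni over three scales would cut power at 46 to 0.65 or need 58. The real downside is that any scale after a non-significant step supports no confirmatory claim, and neither do the tDCS, combination and 2-month results.

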We hypothesize that EC and brain stimulation would decrease disgust experience when exposed to contamination-related stimuli (primary outcome), which, in turn, would improve OCD symptoms (primary outcome). Moreover, since emotional processing can interfere with cognitive functions [41], it is hypothesized that decreases in disgust reactivity would be associated with increases in cognitive functions, particularly in one’s disgust-related attentional bias and inhibitory control (secondary outcomes). We will use electroencephalographic (EEG) characteristics to examine the effectiveness of EC, brain stimulation, and their combined use combination of the (secondary outcome).

Below is a detailed description of the proposed randomized control trial (RCT) following the SPIRIT framework [42].

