#### Conditioned stimuli

In a survey asking people with OCD about contamination concern-related situations and stimuli that elicit disgust and emotion, a list of items was obtained. It included good examples of stimuli to be targeted as CSs. Based on the list, we have collected pictures containing those stimuli. The pictures visibly contained the contamination about OCD people are experiencing concern or obsessions. It might be an exaggeration of real-life situations for some pictures. For example, OCD people show obsessions, “What if the toilet is not completely clean,” even if any dirtiness is obvious, and we had to select a picture of a really dirty toilet to elicit that emotion. These include 30 colorful pictures (e.g., a dirty hand, a muddy face, a pile of unwashed clothes, a dirty sink) rated between − 7.5 to − 10 (mean score= − 9.44) and will be applied in developing an EC training as CSs. Some will also be applied for cognitive tests as emotionally disgusting stimuli.

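### The hypothesis that falling disgust goes with improving cognition concerns change, but the only association analysis named correlates score levels

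*Protocol article*

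**What the plan says.** All references are to the protocol article.

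- **Background, hypotheses:** the authors expect that "decreases in disgust reactivity would be associated with increases in cognitive functions", particularly in disgust-related attentional bias and inhibitory control. These are labelled secondary outcomes.
- **Expected outcomes, text under Table 1:** after the arm-level question for the cognitive tests, the authors say they are also interested in the "correlation of cognitive performance level with the self-reported disgust rating, both at the baseline and after completing interventions". The same text says: "We expect a more significant effect for all measures when the EC training is combined with cathodal tDCS than each one alone".
- **Statistical analysis:** the main method is a mixed and repeated-measures MANOVA "to assess the effect of group (arm) and time and their interactions on the result of EEG recordings, computerized tests, and self-report measures". On adjustment: "The covariates, including age, disgust sensitivity, anxiety, and depression, will be considered in the statistical model".
- **Self-report measures and Expected outcomes:** the Disgust Rating Scale (DRS) is among the measures repeated after baseline, and outcomes are acquired at all three assessments. Change in both scores can therefore be computed.

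The article gives no sample size or power for any correlation.

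**The concern.** The hypothesis is about linked change: patients whose disgust falls more should be those whose cognition improves more. The named analysis relates where patients stand on the two scores, once before and once after treatment. A baseline correlation carries no information on change. A post-treatment correlation mixes any linked change with stable differences between patients that existed before treatment.

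There is a second, conditional problem. The post-treatment correlation is described without reference to arm, and the authors expect the interventions to move all measures. If the arms are pooled, arm effects on the two scores place patients along a common line even when, within every arm, disgust and cognition are unrelated.

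At stake is the reading of the emotion-cognition hypothesis. A significant level correlation could be reported as support for linked change that the data do not show.

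**Working it through.** **1. Does any other analysis fill the gap?** The MANOVA has disgust ratings and cognitive tests on the outcome side and arm, time and their interaction on the predictor side. It estimates what treatment does to each score, not how the two scores are associated. Of the listed covariates (age, disgust sensitivity, anxiety, depression), none is change in disgust. No section names a change-on-change analysis.

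**2. The plan's own figure.** The only sample size is 46 before attrition, for the primary outcomes. It reproduces as the within-between interaction of a repeated-measures MANOVA (Pillai V) with k = 4 arms, m = 3 times, s = min(3, 2) = 2 and f = 0.40:
- λ = f² × N × s = 0.16 × 46 × 2 = 14.72
- df1 = 3 × 2 = 6; df2 = s(N − k − (m − 1) + s) = 2 × 42 = 84
- N = 46 is the smallest total with at least 80% power at 5%.

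It says nothing about the correlation. Completers from 55 enrolled at 20% attrition: 55 × 0.80 = 44.

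**3. Stable differences between patients.** Assumptions, not in the documents: pre-post correlation 0.6 for each score, trait correlation ρ between disgust and cognition, independent changes, no arm effects. The expected level correlation at either visit is 0.6ρ. Results from 20,000 simulated trials, n = 46:

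| ρ | 0.6ρ | Post-treatment level correlation significant | Change correlation significant |
|---|---|---|---|
| 0.3 | 0.18 | 22% | 5% |
| 0.5 | 0.30 | 53% | 5% |
| 0.7 | 0.42 | 84% | 5% |

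This step needs no pooling and no arm effect.

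**4. Arm effects, if arms are pooled.** Assumptions: one intervention (half real, half sham) shifts both scores by d SD in the direction of improvement, both scores coded so that higher is better, with zero within-arm association. Pooled r = 0.25d²/(1 + 0.25d²). For d = 0.8 this is 0.16/1.16 = 0.138. Results from 20,000 simulated trials, n = 44:

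| d | Pooled r | Significant at 5% |
|---|---|---|
| 0 | 0 | 5% |
| 0.5 | 0.059 | 7% |
| 0.8 | 0.138 | 15% |
| 1.0 | 0.200 | 26% |

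If both interventions shift both scores by 0.8 SD, the rate is 39% at n = 46.

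**5. What a remedy needs.** Change scores alone do not remove the arm artefact. With 0.8 SD from each intervention (n = 46, pre-post correlation 0.6), pooled change scores give 51%. Removing arm means from the changes restores 5%.

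Adding the two baselines leaves a small remainder under step 3. With c = 0.6ρ, S = (1 + c) − (0.6 + c)²/(1 + c) and D = (1 − c) − (0.6 − c)²/(1 − c), the partial correlation is (S − D)/(S + D):
- ρ = 0.3: (0.664 − 0.605)/(0.664 + 0.605) = 0.05
- ρ = 0.5: (0.677 − 0.571)/(0.677 + 0.571) = 0.08
- ρ = 0.7: (0.687 − 0.524)/(0.687 + 0.524) = 0.13

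The level correlations in the same settings are 0.18, 0.30 and 0.42.

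**The case against.** **The correlation is an aside, not the declared test.** The article introduces it as something of further interest, and the Discussion restates the cognitive hypothesis largely at arm level, which the MANOVA does address. This stands, and it limits the weight of the point. It does not remove it: the Background states an association between changes as a hypothesis, and the article names one association analysis, which is of another kind.

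**Pooling over arms is not stated.** A reader might infer that the authors will pool. The article is silent, and how an exploratory correlation is stratified is commonly left to the analysis plan. The rates in step 4 are therefore conditional. Step 3 does not depend on them.

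**The sizes rest on assumed shifts.** The documents give no effect size for cognition, and at 0.5 SD from one intervention the rate is close to nominal. This stands.

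**A ceiling on the ratings.** A reader might infer that baseline DRS scores are compressed because the pictures were "rated between − 7.5 to − 10 (mean score= − 9.44". The documents do not support this. The figure comes from a pilot of 15 patients on a bipolar scale from −10 to +10, whereas the DRS runs from 0 to 10, and no between-patient spread on the DRS is given.

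**Adjusting for arm narrows the question.** It removes the disgust reduction that treatment produces. But the MANOVA already tests those arm effects. Whether the two changes go together in patients is a separate question, and answering it requires the arm effects to be removed.

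**Conclusion.** The mismatch between a hypothesis about change and an analysis of levels is in the text, and the MANOVA does not close it. Its size depends on assumptions:

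- With unrelated changes, the level correlation is significant in 22% to 84% of trials of 46 for assumed trait correlations of 0.3 to 0.7.
- Only if arms are pooled, one intervention's assumed effect on both scores of 0.5 to 1.0 SD gives 7% to 26% at n = 44. This applies to the post-treatment correlation alone, since under randomisation the arms cannot create a link at baseline.

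A reader might infer that the trial's main conclusions are at risk. They are not: the hypothesis is secondary and exploratory, and the randomised primary comparisons and the sample size do not rest on it. This is a minor improvement.

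**What to change.** Add one sentence to the Statistical analysis section. The test of this secondary, exploratory hypothesis is a regression of pre-to-post change in each cognitive score on pre-to-post change in DRS, adjusted for arm (four levels) and for the baseline values of both scores. State that the two level correlations are descriptive only. Because of the small remainder in step 5, it is sensible to report the same regression without the baseline terms alongside it.

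Cost: no new data. Five degrees of freedom are spent, three for arm and two for the baselines: with 44 completers, residual degrees of freedom fall from 44 − 2 = 42 to 44 − 7 = 37. Power is limited in any case. At n = 46 a simple correlation of about 0.40 is detectable with 80% power, and about 0.42 after adjustment for arm, so a null result should not be read as evidence of no link. A positive result remains an association and does not establish mediation.
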